### Statistical analyses

The primary analyses will be intention-to-treat (ITT) analyses. Per protocol analyses may also be considered.

Continuous outcomes will be compared between the two intervention groups using the univariate general linear model. If the model assumptions cannot be fulfilled with reasonable approximation a non-parametric test will be used (Mann Whitney). The analysis will be repeated using the baseline variable as a co-variate and the results will be discussed in case of major discrepancies between the two results. Binary outcomes will be compared between the groups using logistic regression. The outcomes will be divided into two classes comprising the primary outcome and all the secondary ones respectively. Dmitrienko et al’s gatekeeping testing procedure with parallel inferences will be used to control the family-wise error rate [46]. All raw P values of all outcome comparisons between the two groups will be presented.

As explorative analyses, all of the above analyses will be repeated with the indicator of comorbid personality disorder as well as the interaction between this indicator and the intervention indicator included. If P of the interaction is ≤ 0.05, an analysis of the corresponding subgroups of patients will be conducted.

If more than 5% of the primary outcome measure is missing, multiple imputation will be used (SPSS version 18 or later). If so, the imputation result will be considered the primary result. This analysis will be supplemented by the following sensitivity analysis. Let A be the group where a beneficial significant effect was observed and B the other group. Missing values in group A will be imputed by the mean value of group B and missing values in group B will be imputed by the mean value of group A. The resulting two distributions will probably not be normal and the variances rather small. So the resulting distributions will be compared using a non-parametric test (Mann-Whitney). This test result will be contrasted to that obtained by comparing the two groups without imputed values also using the non-parametric test.

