### Assessments

Before randomisation: Hamilton Rating Scale for Depression (HDRS) [37], Symptom Checklist 90 Revised (SCL 90-R) [38], Beck’s Depression Inventory (BDI II) [31], World Health Organisation-Five Well-being Index 1999 (WHO 5) [39], Structured Clinical Interviews for DSM-IV Disorders (the depression section of SCID I and SCID II) [30,40], Dimensional Assessment of Personality Pathology-Basic Questionnaire (DAPP-BQ) [41], use of medication, age sex, marital status, and education level.

After 9 weeks of intervention: BDI II WHO 5, use of medication, suicide attempts, and suicides during the intervention period.

After 18 weeks of intervention (end of intensive treatment): HDRS, BDI II, WHO 5, SCL 90-R, use of medication, suicide attempts, and suicides during the intervention period.

After 26 weeks of follow-up treatment: HDRS, SCL 90-R, DAPP-BQ, BDI II, WHO 5, suicide attempts, and suicides during the intervention period.

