### Outcome measure hierarchy

#### Primary outcome measure

- HDRS (after 18 weeks of treatment).

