### Sample size

With a ‘minimal relevant mean difference’ (MIREDIF) between the two compared interventions of 5 HDRS points, an alpha of 0.05 (type I error), a power of 0.90 (type II error of 10%), and a standard deviation (SD) = 7, the sample size calculation shows that a total of 84 participants are necessary. The calculation is performed using the program “Power and sample size calculations”, version 2.1.31.

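### The primary HDRS analysis leads with a model that omits baseline HDRS, repeats it with adjustment, and gives no rule for which result decides

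*Protocol article*

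**What the plan says.** All of this is in the Protocol article.

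- **Lead model (Statistical analyses).** Continuous outcomes are compared between arms with a univariate general linear model. No baseline term is named at this step.
- **Fallback (same section).** "If the model assumptions cannot be fulfilled with reasonable approximation a non-parametric test will be used (Mann Whitney").
- **Adjusted model (same section).** "The analysis will be repeated using the baseline variable as a co-variate and the results will be discussed in case of major discrepancies".
- **Missing data (same section).** Above 5% missing on the primary outcome, multiple imputation is used and its result becomes the primary one. The text does not say whether the imputed analysis includes baseline.
- **Multiplicity (same section).** A gatekeeping procedure runs from the primary outcome to the class of secondary outcomes.
- **Baseline data (Assessments).** "Before randomisation: Hamilton Rating Scale for Depression (HDRS") heads a list that also contains SCL 90-R, BDI II and WHO 5, so all four continuous outcomes have a pre-randomisation value.
- **Randomisation.** The sequence is not stratified.
- **Sample size.** The relevant difference is set "between the two compared interventions of 5 HDRS points", with "a standard deviation (SD) = 7", alpha 0.05 and power 0.90, giving 84 participants. No reduction of the SD for baseline adjustment is mentioned.

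**The concern.** There are three linked weaknesses.

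1. **Order of the models.** The analysis placed first does not use a baseline measurement that the trial already collects. With about 42 per arm and no stratification, adjusting for it would reduce the residual variance at no cost. This matters here because the Discussion concedes that earlier reviews found differences between interventions well below 5 points, and that the small sample raises the risk of random error.
2. **No tie-break.** If the unadjusted and adjusted results fall on opposite sides of 0.05, the only instruction is to discuss it. Gatekeeping needs one primary P value to decide what can be claimed for the secondary outcomes. The imputation rule names a primary result but leaves the same question open.
3. **A fallback that fits the plan poorly.** The relevant difference is a difference in means. Mann-Whitney does not estimate one and takes no covariate, so the planned adjusted repeat has no rank counterpart if the switch is made. A rank test also has no standard pooled estimate after multiple imputation.

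**Working it through.** **Inputs from the article:** difference 5, SD 7, alpha 0.05, power 0.90, 1:1 allocation, 84 in total (42 per arm).

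**Assumed:** the correlation r between baseline and week-18 HDRS, which the article does not give. The main range is 0.2 to 0.5. Data are taken as normal with equal SDs and none missing.

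**Step 1: reproduce the plan's figure.** Two-sided normal approximation:

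n per arm = 2 × (1.960 + 1.282)² × 7² / 5² = 2 × 10.51 × 1.96 = 41.2, rounded up to 42, so 84 in total.

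This matches. Sidedness is not stated, but one-sided 0.05 would give 68, so two-sided is inferred. Power at 42 per arm is 0.905 by the normal approximation and 0.899 by the noncentral t with 82 df. The 84 therefore belongs to the unadjusted test.

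**Step 2: effect of adjusting.** Residual SD = 7 × √(1 − r²). The standard error of the difference is that SD × √(2/42). Power is from the noncentral t with 81 df (82 unadjusted). The CI half-width is the t quantile (about 1.99) × SE. Unadjusted: SE = 7 × 0.2182 = 1.528, and half-width = 1.99 × 1.528 = 3.04.

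| r (assumed) | Variance removed (r²) | Residual SD | Power at 5 points | Power at 3 points | 95% CI half-width |
|---|---|---|---|---|---|
| unadjusted | – | 7.00 | 0.899 | 0.49 | 3.04 |
| 0.2 | 4% | 6.86 | 0.910 | 0.51 | 2.98 |
| 0.3 | 9% | 6.68 | 0.924 | 0.53 | 2.90 |
| 0.4 | 16% | 6.42 | 0.942 | 0.56 | 2.79 |
| 0.5 | 25% | 6.06 | 0.962 | 0.61 | 2.63 |

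The formula ignores the small cost of estimating the slope under chance imbalance. A simulation of 20,000 trials per setting gave adjusted power at 5 points of 0.922 (r = 0.3) and 0.960 (r = 0.5), so that cost is negligible.

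**Step 3: how often the two models disagree.** In the same simulation, the unadjusted and adjusted tests fell on different sides of 0.05 in this share of trials:

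- True difference 3 points: 10% (r = 0.3) and 19% (r = 0.5).
- True difference 5 points: 4% and 7%.

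**Step 4: does the switch of test do harm by itself?** With no true difference, the unadjusted test rejected in 4.8% to 5.0% of trials and Mann-Whitney in 4.8% to 5.1%. A Shapiro-Wilk-driven switch between the two (5,000 trials per setting) rejected in 4.5% to 5.3%. Mann-Whitney power at 5 points was 0.88 to 0.89. Under normal data the switch does not inflate type I error and costs little power. The case against it is the change of target and the loss of the covariate.

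**The case against.** The strongest reply is that the plan is valid as written. Randomisation justifies the unadjusted comparison, its standard error already allows for chance imbalance, and the sample size was computed for it. The adjusted model is prespecified, the statistician works with arms coded A and B, and all raw P values will be presented. All of this stands, and it limits the point in several ways.

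- A reader might infer that the trial **ignores baseline**. It does not; only the lead comparison omits it.
- A reader might infer that there is **no primary result**. The order of the text implies that the unadjusted model leads, and the missing-data rule names a primary result. What is absent is an explicit statement and a tie-break.
- A reader might infer that **three P values compete in the gatekeeping**. Mann-Whitney replaces the linear model and does not sit beside it, and nothing says the adjusted repeat may enter. If the more favourable of the unadjusted and adjusted tests could be taken, simulated type I error would be 6.3% at r = 0.3, but the article does not permit that choice.
- A reader might infer **a shortfall against 90% power**. Step 1 shows there is none.

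Two further replies have partial force. First, the gain rests on an unknown correlation, and selecting patients on BDI II above 13 may narrow the baseline range and lower it; at r = 0.2 the gain at 5 points is only about one percentage point of power. Second, a mean difference could be reported next to a rank test. That would still leave the deciding P value detached from the reported estimate. Coding the arms hides the direction of effect, but not which model gives the smaller P value.

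The missing numerical criterion for acceptable model assumptions may sit in a fuller plan and is not held against the article. The order of the models and the instruction to discuss discrepancies are stated in the article itself, so they are not mere omissions.

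**Conclusion.** The point holds as a matter of efficiency and clarity, not validity. The less precise model leads, no rule settles a disagreement with the adjusted one, the adjustment status of the imputed primary result is unstated, and the fallback test cannot address the mean difference for which the trial was sized.

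The size depends on r. Over the assumed range of 0.2 to 0.5, power rises by 1 to 6 percentage points at 5 points and by 2 to 12 at 3 points, and the confidence interval narrows by about 2% to 13%. At the low end this is a minor gain; at the high end it is worth 84 / (1 − 0.25) = 112 participants under the unadjusted analysis. The figures assume normal data, a common SD of 7 and no missing week-18 values. The change should be made because it is free, not because the present analysis is wrong.

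**What to change.** Before unblinding, and preferably before any coded A/B comparison is run, state the following.

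- The single primary analysis is the linear model of week-18 HDRS on treatment with baseline HDRS as covariate. The same model is used within multiple imputation if that is triggered.
- If model assumptions are doubtful, robust standard errors are used in place of a change of test.
- The adjusted mean difference is reported with its 95% CI, and only its P value enters the gatekeeping as the primary test.
- SCL 90-R, BDI II and WHO 5 are analysed in the same way, each with its own baseline.
- The unadjusted model and Mann-Whitney are kept as sensitivity analyses that cannot replace the primary result.

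The logistic model for remission is left out of this change: adding baseline HDRS there would alter the target to a conditional odds ratio, which is a separate decision.

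The cost is a few sentences. No new data are needed, and both linear models are already planned.

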We have chosen to classify our control intervention as ‘mentalization-based therapy’. This intervention was, as mentioned, originally designed to treat borderline personality disorder but is now used in a number of different clinical settings symptoms [25,26]. As we except about 80% of the participants will have comorbidity of depression and personality disorder [53], we believe that mentalization-based therapy will be a relevant control intervention. Mentalization-based therapy is a relatively new intervention and we did not identify any relevant treatment manual we could use. We chose to create our own treatment manual, but due to limited resources the mentalization-based manual became relatively short. The content of the control intervention is therefore less strictly defined and this is a further limitation of this trial.

After the initial 18 weeks of intervention, both intervention groups will be offered a follow-up intervention (1 weekly group session). This follow-up intervention will due to limited resources not be manualised and adherence to treatment manual will not be assessed. The results from the follow-up intervention will be difficult to interpret because the form and content of the both follow-up interventions will be unclear. Furthermore, since the participants will be free to leave the trial after the 18 weeks of intensive treatment (before the follow-up treatment begins), it might be unclear if a certain group of patients will be systematically excluded from the analysis and this might cause biased long-term follow-up results. The participants are free to leave the trial at any time point but based on our experience, we expect a relatively large number of participants to be lost to follow up after the 18 weeks of intensive treatment.

Interventions for depression have until now shown relatively small effect sizes. We want to examine two modern psychotherapeutic methods — and we hope that the results from this trial can contribute to new knowledge about effective interventions for depression.

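### The mean-swap sensitivity analysis is worded around a significant result, can only pull the difference toward zero, and does not test the multiple-imputation result that the plan calls primary

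*Protocol article*

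**What the plan says.** The protocol article, under Statistical analyses, compares continuous outcomes with a general linear model, with Mann-Whitney as the fallback if the assumptions fail. On missing data it states: "If more than 5% of the primary outcome measure is missing, multiple imputation will be used". The imputation result then becomes the primary result.

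One sensitivity analysis supplements it. Its groups are set by the outcome of the trial: "Let A be the group where a beneficial significant effect was observed and B the other group". The rule is "Missing values in group A will be imputed by the mean value of group B", and missing values in B receive the mean of A. The section expects the resulting distributions to be non-normal with rather small variances, and for that reason compares them with Mann-Whitney. The result is set beside a Mann-Whitney test of the observed values alone. No rule is given for the case where neither arm shows a significant benefit, nor for how a discrepancy is to be read.

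**The concern.** A sensitivity analysis for missing data should show how far the reported result depends on the assumption behind the imputation. This one falls short in three ways.

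- **It is worded through significance.** Group A exists only if an arm has shown a significant benefit, so the text prescribes no check for a null result. The Discussion concedes that the 5-point difference could be called unrealistically high and that earlier reviews found much smaller differences, so a null result is a realistic outcome.
- **It works in one direction.** Each arm's missing values are replaced by the other arm's mean, which brings the arms together. If dropout has hidden a real difference, the swap cannot reveal it.
- **It tests a different analysis.** Above 5% missing, the primary result comes from multiple imputation. The swap compares one Mann-Whitney test with another. Neither gives a mean difference with a confidence interval in HDRS points, and replacing missing values by one constant leaves out imputation uncertainty.

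At stake is whether readers can tell if the primary conclusion holds under plausible non-ignorable dropout.

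**Working it through.** **Inputs.** From Sample size: a difference "between the two compared interventions of 5 HDRS points", "a standard deviation (SD) = 7", alpha 0.05 and power 0.90. From Design & methods: 84 patients randomised 1:1, about 42 per arm. The protocol gives no week-18 missing share, so a range is assumed.

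**The plan's own figure.** Two-sided normal approximation: n per arm = 2 × (1.960 + 1.282)² × 7² / 5² = 2 × 10.51 × 49 / 25 = 41.2, rounded up to 42, or 84 in total. The stated sample size reproduces.

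**When the check applies.** 5% of 84 is 4.2, so imputation and its sensitivity analysis begin at 5 missing values. Two missing per arm (4/84 = 4.8%) is below the trigger; 4 per arm (8/84 = 9.5%) is above it.

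**Algebra of the swap.** Let a and b be the observed arm means and mA and mB the missing fractions.

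- Mean of A after the swap: (1 − mA)a + mA·b
- Mean of B after the swap: (1 − mB)b + mB·a
- Difference: (1 − mA − mB)(a − b)

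While mA + mB is below 1, the difference shrinks and keeps its sign. The factor depends only on how many values are missing, not on who is missing. Exchanging the labels A and B leaves the imputed data unchanged.

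**Unbiased dropout, true difference 5.** Simulated trials had 42 per arm, normal scores, SD 7, equal missingness completely at random and two-sided Mann-Whitney at 0.05. The last column is the share of significant completers' results that stay significant after the swap.

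| Missing per arm | Factor 1 − 2m | 5 points become | Still significant |
|---|---|---|---|
| 4/42 | 0.81 | 4.0 | about 85% |
| 6/42 | 0.71 | 3.6 | about 69% |
| 8/42 | 0.62 | 3.1 | about 46–48% |
| 10/42 | 0.52 | 2.6 | about 20% |
| 13/42 | 0.38 | 1.9 | about 2% |

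Independent runs agree to within two or three percentage points.

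**Larger true effects.** At 8/42 per arm, about 78% survive for a true difference of 7 and 96% for 9. At 13/42, about 8% and 27% survive.

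**Biased dropout, no true difference.** Remove 8 of 42 at random from the worse-scoring half of one arm and none from the other. The completers' test then falsely favours that arm in about 13% of trials, against a nominal 2.5%. The swap leaves about 55–57% of these false positives significant, so surviving it does not show that dropout played no part.

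**The case against.** The strongest defence is that the swap only supplements multiple imputation. Nothing lets it override the primary estimate, and multiple imputation runs whether or not the result is significant, so dropout explained by observed data is covered for a null result too. Comparing Mann-Whitney with Mann-Whitney is like for like and isolates the effect of filling in values. The remark about non-normality and small variances is the plan's reason for a rank test, not an admission of error. A single harsh scenario is a legitimate choice. All of this stands and keeps the severity low. It does not supply a check on the imputation model or a look in the direction away from zero.

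Three stronger readings are tempting, and the document does not support them.

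- **A reader might infer that the swap overturns true effects by construction.** Only the shrinkage is built in. Loss of significance depends on the missing share and the effect: most results survive at 4/42 per arm, and at 8/42 most survive if the true difference is 7 or 9.
- **A reader might infer that the check cannot be carried out for a null result.** The wording leaves that case open, but the swap is symmetric and can be computed for any result. That part is a drafting gap. The substantive limit is that it moves only toward zero.
- **A reader might infer that imputation is planned only for the primary outcome and that all others are analysed on completers.** The 5% trigger refers to the primary outcome and the article is silent on the rest. In a condensed article whose full analysis plan is not shown, that silence is not a finding. The Discussion's statement that "we expect a relatively large number of participants to be lost to follow up after the 18 weeks of intensive treatment" does not fill the gap either: the primary and secondary outcomes are all measured at 18 weeks, and the article already warns that the later results may be biased.

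**Conclusion.** The concern holds as a cheap improvement to a supplementary analysis; it is not an essential correction. The sensitivity analysis is defined through a significant result, shrinks the difference by 1 − mA − mB, and is not a test of the imputation model whose result is primary. It cannot show whether a null result is due to non-ignorable dropout, and it can leave standing a positive result that dropout created.

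At the planning difference of 5 points with unbiased dropout, survival of significance falls from about 85% with 4/42 missing per arm to about half with 8/42 and about 2% with 13/42. These figures rest on normal scores with SD 7, 42 per arm, equal missingness completely at random, and missing shares that are assumed. If week-18 loss turns out small or the true effect large, the practical consequence is slight.

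**What to change.** Replace or supplement the mean swap with a delta-adjusted (tipping-point) version of the same multiple-imputation linear model for week-18 HDRS:

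- Shift the imputed values by 0 to 5 points, the plan's own minimal relevant difference, separately by arm and in both directions.
- Report the mean difference and confidence interval at each shift, and the shift, if any, at which the conclusion changes.
- Run it whenever multiple imputation is used, whether or not the primary result is significant.
- Use the week-9 BDI II and WHO 5, which Assessments already schedules, as auxiliary variables in the imputation model.

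If the swap is kept beside this, define it without reference to significance; its symmetry makes that a change of wording only. The cost is some extra programming and a further table to report. No new data are needed.

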### Prevention of missing values

The primary investigator will ensure that all questionnaires will be completed and will be present at the location where the participant assessments take place. The primary investigator and a research secretary will independently check if all participants have been rated at the relevant time points.

All participants will, in good time, be invited in written letter to participate in the assessments. If the trial participants do not show up or cancel, they will be invited to another assessment. In such circumstances the trial participants will be invited at least three times to a given assessment, and will be contacted on phone or by mail. A research secretary ([name]) will try to solve any problem that hinders the participant in showing up to the assessment.

### Ethical considerations and regulatory approval

There are no immediate ethical problems regarding this trial. Research has not identified any significant adverse effects or risks from either of the compared interventions — and we do not know which is the best intervention. During the trial period any adverse event will be reported. The trial has obtained approval by the Regional Ethics Committee of Zealand (no: SJ-43), and is registered at the Danish Data Protection Agency (no: 2008-58-0020).

Participants will be informed of the trial in writing and verbally, and written informed consent will be obtained from every participant before inclusion. All trial participants may, on request, be permitted access to further information about the project. The individual therapists and the principal investigator will perform this function. No expense allowance is offered to trial participants.

